#### Exclusion criteria

Exclusion criteria for participation are delirium on admission according to the DSM-IV criteria; VMS 0; patients not able to take study medication according to protocol (including nil per os); specific heart conditions on admission including QTc interval of more than 500 ms, recent myocardial infarction, decompensated heart failure, second- or third-degree AV block, (history of) ventricular arrhythmias or Torsade de Pointes (TdP), uncorrected hypokalemia with serum potassium level 3.0 milliequivalents per liter (mEq/L) or less, clinical significant bradycardia; concomitant use of pharmacodynamically interacting medication; use of antipsychotic or dopaminergic drugs; use of QT prolonging drugs in the presence of prolonged QTc interval (more than 450 ms and 460 ms, for men and women respectively) on baseline ECG; Parkinson’s Disease; Vascular or Lewy Body Dementia; Hypokinetic Movement Disorder; (history of) Neuroleptic Malignant Syndrome; Central Anticholinergic Syndrome; substance abuse and dependence according to the DSM-IV criteria; (history of) epilepsy; concomitant participation in another clinical trial with the exception of observational studies; not competent to provide informed consent.

### Randomisation

Two well-known variables associated with increased risk of delirium are age 80 years or over and surgical treatment/anaesthesia. To balance population representatives in both treatment groups, four strata are constructed with separate randomisation schedules: (1) age 70 to 80 years, planned surgery on admission; (2) age 70 to 80 years, no planned surgery on admission; (3) age 80 years or over, planned surgery on admission; (4) age 80 years or over, no planned surgery on admission. Each stratum consists of 20 pre-randomised individual study numbers, 10 assigned to haloperidol and 10 to placebo treatment, prepared by the Central Pharmacy for The Hague Hospitals (Apotheek Haagse Ziekenhuizen/AHZ located in The Hague, the Netherlands). Participants, observers, physicians, nurses, other care givers, at the investigative sites are all blinded to the assigned intervention. The VUmc clinical pharmacy holds the randomisation list.

### Study interventions

AHZ is responsible for preparing, labelling, packaging and distributing the study medication according to Good Manufacturing Procedure (GMP) guidelines. Both the haloperidol (as a verum) and placebo tablets are identical in appearance, have fixed concentrations of 1 mg per tablet, and are packaged in identically labelled medicine carton boxes. Study medication prescription is standardised in every study centre’s automated prescription system. On prescription by the local investigator(s), a carton box containing study medication (either haloperidol or placebo tablets) can be collected. To ensure study medication access 24 hours a day, seven days a week, medicine boxes are securely stored in the ED or on the wards rather than in the local clinical pharmacy.

### Data collection

Data will be mainly collected by two observers, a physician ([name]) and geriatric nurse [name] trained according to the Good Clinical Practice (GCP) principles. Participants’ demographic data, medical history, (prescription) medication history on admission (including the use of sleep medication and antidepressants), presence of sleep-wake cycle disturbances, visual and/or hearing impairment, substance use, and vital parameters will be documented. Medical history and (prescription) medications will be coded according to the World Health Organization’s International Statistical Classification of Diseases and Related Health Problems 10^th^ revision (ICD-10)
[16], and the Anatomical Therapeutic Chemical (ATC) Classification System
[17]. Severity and number of co-morbidities are listed according to the Charlson comorbidity index using the ICD-10 coding algorithm
[18,19]. Physical function is assessed with the Katz Index of Independence in Activities of Daily Living (ADL)
[20,21] and the Lawton Instrumental Activities of Daily Living (IADL) scale
[22]. The Six Item Cognitive Impairment Test (6-CIT) is used to evaluate participants’ cognitive function
[23-25]. Primary caregivers are asked to complete the IQCODE-N in order to reflect on the participant’s cognitive function prior to hospitalisation
[26]. The Confusion Assessment Method (CAM) will be used to diagnose delirium according to the Diagnostic and Statistical Manual of Mental Disorders, Fourth edition (DSM-IV) delirium criteria during the study intervention period, and to ensure delirium is not present on study inclusion
[27]. Nurses register the Delirium Observation Screening (DOS) scale three times a day (once every day, evening and night shift) during the intervention period to evaluate delirium symptoms
[28,29]. Once delirium is established, one of the observers will perform the DRS-R-98 once-daily to assess delirium severity and duration
[30]. An ECG is performed at baseline, after two and six treatment dosages, and at the end of the intervention period to register QTc intervals. ECG is repeated daily until a steady state is reached in case of prolonged QTc interval (more than 450 ms and 460 ms, for men and women respectively), or if the patient is taking other QT prolonging medications. On study inclusion, and at the time of ECG after study drug administration dose six, a 4 ml blood sample is collected, and plasma is stored at -80°C at the VUmc Clinical Pharmaceutical and Toxicological Laboratory to determine haloperidol levels. On discharge, the number of days spent in the hospital is recorded.

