#### Secondary outcome measures

Severity and duration of delirium; number of delirium-free days; hospital length-of-stay; adverse events; all-cause mortality in-hospital and within six months post-discharge; cognitive and physical function at baseline, three, and six months post-discharge; new institutionalisation post-discharge; number of hospital admissions within six months post-discharge.

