With respect to delirium, the VMS program based standardised hospital care covers identification and modulation of precipitating delirium risk factors such as medication reviews and orientation and noise-reduction measures, creating an optimal background regimen for conduction of this trial in all participating hospitals. Patients who positively confirm one or more of the VMS delirium risk questions (VMS ≥1) are considered at-risk for developing delirium during hospital admission. Patients with VMS 0 on first evaluation are not eligible for this study. Eligible patients will be asked for informed consent. In case of inability to write, patients must provide verbal consent in the presence of an independent witness (preferably patients’ proxy) who may then sign the informed consent form. The study medication, haloperidol 1 mg or identical placebo tablets, will be given orally to participants twice daily at 12 pm and 8 pm for a maximum of seven consecutive days (14 treatment dosages) on top of standardised care based on the implemented VMS program ‘Vulnerable elderly’. During the seven-day intervention period nursing staff will screen participants for delirium symptoms. Additionally, a trained observer (physician or geriatric nurse) will daily visit participants to detect the presence of delirium, register potential adverse events based on 24-hour nursing observations, clinical judgement, and electrocardiogram (ECG) monitoring, and to check for adherence to standardised adequate environmental manipulations for delirium such as orientation measures. For patients who have not developed delirium within seven days of initiation of the study intervention, daily assessment stops. Patients who develop delirium are evaluated daily by the observer to record delirium severity and duration until symptoms diminish. Study drug administration is terminated early if a participant develops delirium, is transferred to a non-participating care unit such as the ICU, refuses further participation in the trial, the QTc interval is more than 500 milliseconds (ms), is discharged from the hospital, or dies within seven-day of initiation of the study intervention. In case of established delirium or if the assigned study intervention is thought to have a direct influence on the patient’s treatment, the treating physician will request for unblinding and may further decide on treatment. For unblinding of treatment assignment, the treating physician is able to contact the VUmc consultant pharmacist through a central telephone number 24 hours a day, seven days a week.

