### Sample size calculation

The primary study objective is to evaluate the effect of prophylactic haloperidol compared to placebo for the incidence of in-hospital delirium within seven days of start of the study intervention. Based on previous studies, we expect the incidence of delirium in our target patient population currently to be 20%. Aiming for an absolute reduction of 10% in the haloperidol intervention group, with the significance level set at 5%, inclusion of n = 195 patients per study arm (390 patients in total) will give us a power of 80% to detect differences with a two-sided alpha of 0.05.

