### Statistics

For the data analysis IBM SPSS Statistics 20 will be used. Clinical trial data will be primarily registered in paper case report forms and later transcribed into the electronic data capture system of OpenClinica, open source clinical trail software. The primary analysis is aimed at evaluation of the primary outcome of this study: the incidence of in-hospital delirium according to the DSM-IV criteria in older at-risk patients aged 70 years or over who are acutely admitted through the ED for a general medicine or surgical specialty within seven days of initiation of the study intervention. Data from all randomised patients will be analysed according to the Intention-to-treat principal. The primary outcome delirium incidence is considered a binary outcome, present or absent. Patients who for example leave the hospital (or die in-hospital) within seven days of start of the study intervention without experiencing delirium will be regarded negative on the primary outcome. Patients who do not complete the intervention will be monitored during their in-hospital stay for occurrence of delirium. The number of patients diagnosed with delirium at least once in the seven days following initiation of the study intervention will be calculated for both the haloperidol and placebo group, and subsequently this number is divided by the total amount of patients assigned to the matching group, reflecting in-hospital delirium incidence ratio within seven days of initiation of the study intervention. Pearson’s chi-squared test will be used to compare this number between the two groups. Continuous normally distributed data including patient demographic data will be tested with Student’s *t* test. The Mann–Whitney *U* test is used for comparison of non-normal distributed data such as secondary outcome measures concerning efficacy of prophylactic haloperidol treatment. Log rank test will be used to establish the time to (first) delirium diagnosis (number of delirium-free days), which will be compared between groups. Adverse events in both groups will be globally described. Kaplan-Meier estimates will be used to display survival probability within 6 months after hospital discharge for patients with and without diagnosed in-hospital delirium.

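### DRS-R-98 severity is scored only in patients who become delirious, so its between-arm test compares subgroups defined by the primary outcome; the same holds for duration if non-delirious patients are left out

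*Protocol article*

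**What the plan says.** Three parts of the protocol article together determine the comparison.

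- **Outcomes.** The list of secondary outcome measures opens with "Severity and duration of delirium; number of delirium-free days".
- **Measurement.** Data collection states: "Once delirium is established, one of the observers will perform the DRS-R-98 once-daily to assess delirium severity and duration". Study design, in the text after Figure 2, agrees: "Patients who develop delirium are evaluated daily by the observer to record delirium severity and duration until symptoms diminish". For patients still free of delirium after seven days, the daily visits end. No DRS-R-98 is planned for them.
- **Analysis.** The Statistics section says that the Mann-Whitney U test "is used for comparison of non-normal distributed data such as secondary outcome measures concerning efficacy of prophylactic haloperidol treatment". It commits to intention-to-treat for all randomised patients. For the primary outcome it also gives an explicit rule: patients who leave or die without delirium count as negative. It gives no such rule for severity or duration.

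The Sample size calculation expects 20% incidence and adds: "Aiming for an absolute reduction of 10% in the haloperidol intervention group".

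**The concern.** A severity score exists only for someone who has had the primary outcome event, and the treatment is intended to prevent that event. If it works as planned, the delirious placebo group contains everyone prone to delirium, while the delirious haloperidol group contains only those in whom prophylaxis failed. These two groups need not be alike at baseline, and stratified randomisation does not make them alike.

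A difference in DRS-R-98 between them could therefore come from the drug acting on severity, from the drug changing who is left to be measured, or from both. The data cannot separate these. Severity and duration stand first among the secondary outcomes, and the Discussion says that they influenced the length of the intervention period. A reader is therefore likely to take a significant Mann-Whitney result as a treatment effect on severity.

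**Working it through.** **Inputs.** From the Sample size calculation: 195 per arm, 20% v 10% incidence, 80% power, two-sided alpha 0.05. From the Discussion: in the cited 430-patient hip-surgery trial, highest DRS-R-98 was 18.4 (SD 4.3) on placebo and 14.4 (SD 3.4) on haloperidol. The SD of 4.3 is borrowed here as an assumption.

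**1. The plan's own figure.** With unpooled variance, n = (1.960 + 0.842)² × (0.20×0.80 + 0.10×0.90) / 0.10² = 196.2 per arm. The arcsine formula gives 194.9 and the pooled formula 199. Power at 195 per arm is 79.2%. The stated sample size reproduces and is not at issue.

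**2. Who is compared.** Placebo: 195 × 0.20 = 39. Haloperidol: 195 × 0.10 = 19.5. Together that is 58.5 of 390, or 15% of those randomised, in a 2:1 ratio created by the treatment effect.

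**3. Spurious difference.** Assume that haloperidol prevents half of the delirium that would occur on placebo, causes none, and changes nobody's severity. Take severity as normal with SD 4.3. Let ρ be the correlation between severity and the tendency to remain delirious on haloperidol. Keeping the upper half of that tendency shifts mean severity by

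ρ × SD × √(2/π) = ρ × 4.3 × 0.798 = 3.43ρ points (haloperidol minus placebo).

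The last column is the simulated Mann-Whitney rejection rate at a nominal 5% (4,000 runs each, ρ ≥ 0 only).

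| ρ | Spurious difference (points) | Rejection rate |
|---|---|---|
| −1 | −3.4 | as for +1, by symmetry |
| −0.5 | −1.7 | as for +0.5 |
| −0.3 | −1.0 | as for +0.3 |
| 0 | 0 | 4.6% |
| 0.3 | +1.0 | 13% |
| 0.5 | +1.7 | 29% |
| 1 | +3.4 | 91% |

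For scale, the cited trial's difference was 18.4 − 14.4 = 4.0 points.

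**4. Precision.** With 39 v 19.5 patients, the difference detectable with 80% power is about 2.802 × √(1/39 + 1/19.5) = 0.78 SD, or 0.78 × 4.3 ≈ 3.3 points. A true effect on severity would have to be large to show, even without selection.

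**5. Ranking everyone on severity.** Give non-delirious patients the lowest severity value and compare 195 v 195. Simulated rejection (2,000 runs) is 4.8% when the arms do not differ. It is 79% at 20% v 10% incidence with equal severity among the delirious. That is essentially the power of the primary comparison (79.2%), so this analysis keeps the randomisation but largely repeats the incidence test.

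**The case against.** **The restriction is inferred.** No sentence says that severity or duration is compared only among delirious patients, and a statistical analysis plan that is not shown may define the analysis set. This has force for duration. All participants are visited daily during the intervention period, so 0 days can be assigned to those observed without delirium, and what is lacking is only a scoring rule. It has little force for severity. The article itself fixes who is scored and which test is used, and the intention-to-treat sentence cannot supply scores that are never collected.

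**Other measures cover everyone.** Delirium-free days are analysed as time to first delirium, and nurses record the DOS scale three times a day during the intervention period. Both are true, but neither replaces DRS-R-98 severity.

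**The bias may be nil.** This stands. If haloperidol does not change who becomes delirious, or if prevention is unrelated to severity, there is no spurious difference.

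A reader might go further and infer that haloperidol will be made to look harmful, that the bias must grow as the drug works better, or that 3.4 points is the expected size. The documents support none of these. No section says that mild cases are prevented first. At ρ = 0 there is no bias at any efficacy, and a negative ρ flatters the drug. The 3.4-point figure requires prevention to depend on severity alone. The 4.0-point benchmark comes from a trial that, by the article's own account, did not significantly reduce incidence.

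**Conclusion.** The point holds for severity as the plan is written: the Mann-Whitney test can only compare about 20 delirious haloperidol patients with 39 delirious placebo patients, and randomisation does not protect that contrast. It holds for duration only if duration too is compared among delirious patients, which the Statistics section leaves open.

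The size of the bias is unknown. Under halved incidence, no individual effect on severity, normal scores and an SD of 4.3, it lies between −3.4 and +3.4 points and is zero at no correlation. Neither its size nor its sign can be recovered from the trial data, because the correlation is not observed.

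Two secondary outcomes are affected. The primary outcome, delirium-free days and the sample size are not.

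**What to change.** In the Statistics section:

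1. Compare days with delirium between arms in all randomised patients, with 0 days for those without delirium. State the period counted, since daily visits end at seven days for patients without delirium but continue for those with it. State a rule for death and early discharge.
2. Report DRS-R-98 severity and duration among delirious patients as descriptive. Label them as conditional on a post-randomisation event and not as evidence of a causal effect on severity.
3. Optionally, add an all-randomised rank analysis of severity, with the lowest rank for no delirium. Call it supportive and say that it measures incidence and severity together.

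**Cost.** This changes wording only: no new patients, visits or measurements. The downside is that the all-randomised estimates mix incidence with duration or severity and can be significant through incidence alone. The descriptive figures should therefore stay beside them.

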### Follow-up assessments

Three and six months after discharge, patients are contacted by telephone by one of the observers to perform the Katz ADL, the Lawton IADL scale, and the 6-CIT, and to obtain data on home residency, hospital admissions, (recurrent) delirium, and all-cause mortality.

### Study monitoring

This study will be monitored by two members – the manager and an independent clinical research assistant – of the Clinical Research Unit, Department of Internal Medicine, VUmc Amsterdam, the Netherlands. During the monitoring visits at respectively the beginning, half-way and end of the study, the consistency of data collection, documentation and the presence and completeness of the Investigator Site File are checked for compliance with GCP guidelines. Findings are systematically recorded and signed by the monitors.

### Data Safety Monitoring Board

Because this study is a pharmacological intervention study recruiting (vulnerable) older patients, we appointed a Data Safety Monitoring Board (DSMB). The primary mandate of the DSMB is to monitor patient safety during the trial. The DSMB for this study consists of four independent members: two emeritus professors of internal medicine, a professor of clinical epidemiology, and a consultant physician in geriatric medicine. The DSMB reviews unblinded results and convenes prior to the beginning of the study, and thereafter, every six months from the first randomisation date. On request, the DSMB may obtain unblinded study results from the hospital pharmacy. When a study participant dies, the DSMB evaluates the event and mortality rates in both study arms. After 125 patients have completed the entire study period including follow-up in each study arm, the DSMB will perform a safety interim analysis with respect to all-cause mortality.

### Sample size calculation

The primary study objective is to evaluate the effect of prophylactic haloperidol compared to placebo for the incidence of in-hospital delirium within seven days of start of the study intervention. Based on previous studies, we expect the incidence of delirium in our target patient population currently to be 20%. Aiming for an absolute reduction of 10% in the haloperidol intervention group, with the significance level set at 5%, inclusion of n = 195 patients per study arm (390 patients in total) will give us a power of 80% to detect differences with a two-sided alpha of 0.05.

### Statistics

For the data analysis IBM SPSS Statistics 20 will be used. Clinical trial data will be primarily registered in paper case report forms and later transcribed into the electronic data capture system of OpenClinica, open source clinical trail software. The primary analysis is aimed at evaluation of the primary outcome of this study: the incidence of in-hospital delirium according to the DSM-IV criteria in older at-risk patients aged 70 years or over who are acutely admitted through the ED for a general medicine or surgical specialty within seven days of initiation of the study intervention. Data from all randomised patients will be analysed according to the Intention-to-treat principal. The primary outcome delirium incidence is considered a binary outcome, present or absent. Patients who for example leave the hospital (or die in-hospital) within seven days of start of the study intervention without experiencing delirium will be regarded negative on the primary outcome. Patients who do not complete the intervention will be monitored during their in-hospital stay for occurrence of delirium. The number of patients diagnosed with delirium at least once in the seven days following initiation of the study intervention will be calculated for both the haloperidol and placebo group, and subsequently this number is divided by the total amount of patients assigned to the matching group, reflecting in-hospital delirium incidence ratio within seven days of initiation of the study intervention. Pearson’s chi-squared test will be used to compare this number between the two groups. Continuous normally distributed data including patient demographic data will be tested with Student’s *t* test. The Mann–Whitney *U* test is used for comparison of non-normal distributed data such as secondary outcome measures concerning efficacy of prophylactic haloperidol treatment. Log rank test will be used to establish the time to (first) delirium diagnosis (number of delirium-free days), which will be compared between groups. Adverse events in both groups will be globally described. Kaplan-Meier estimates will be used to display survival probability within 6 months after hospital discharge for patients with and without diagnosed in-hospital delirium.

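### Randomisation is stratified by age and planned surgery but the primary chi-squared test ignores the strata: valid, mildly conservative, and a little power given up

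*Protocol article*

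**What the plan says.** The Randomisation section of the protocol article gives the reason for stratifying: "Two well-known variables associated with increased risk of delirium are age 80 years or over and surgical treatment/anaesthesia". To balance the arms on these, "four strata are constructed with separate randomisation schedules", formed by crossing the two age groups with planned surgery on admission (yes or no). Each stratum is supplied with 20 study numbers, 10 per treatment.

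The Statistics section defines the primary outcome as binary, divides the number of patients with delirium by the number assigned to each arm, and fixes the test: Pearson's "chi-squared test will be used to compare this number between the two groups". No stratified or covariate-adjusted analysis appears there. The log-rank test for time to first delirium is also named without strata.

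The Sample size calculation section uses a crude comparison of 20% with 10% and 195 patients per arm, which "will give us a power of 80% to detect differences with a two-sided alpha of 0.05".

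**The concern.** When allocation is balanced within strata that predict the outcome, differences between strata contribute little to the random variation of the treatment difference. Pearson's pooled variance, p(1 − p) at the overall event rate, still counts them. The test statistic therefore varies less than its reference distribution assumes. The test rejects a true null less often than 5% and is slightly less sensitive to a real effect than a test that uses the strata.

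What is at stake is efficiency and agreement between design and analysis. The protocol chose the strata on the ground that they are prognostic, and on that premise the pooled test leaves some of the benefit unused. It is also a choice best settled before unblinding, because a later move to a stratified test could look driven by the data.

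**Working it through.** **1. Inputs from the protocol article.** Control rate 20%, haloperidol rate 10%, 195 per arm, two-sided alpha 0.05, power 80% (Sample size calculation). Four strata with 10:10 allocation per 20 numbers (Randomisation). Pooled Pearson test (Statistics).

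**2. The plan's own sample size.** With pooled variance under the null and no continuity correction,

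n = [1.96·√(2·0.15·0.85) + 0.8416·√(0.16 + 0.09)]² / 0.10² = (0.990 + 0.421)² / 0.01 ≈ 199 per arm.

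With unpooled variance, n = (1.96 + 0.8416)²·(0.16 + 0.09) / 0.01 = 196.2, so 197. Both lie within 3% of 195. Power at 195 is Φ[(√195·0.10 − 0.990) / 0.5] = Φ(0.813) = 79.2%. The stated figure therefore reproduces, and the calculation is consistent with the crude test.

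**3. Assumptions the protocol does not supply.** Stratum shares: 10% aged 70 to 80 with planned surgery, 40% aged 70 to 80 without, 10% aged 80 or over with, 40% aged 80 or over without. Prognostic strength: the same odds ratio (OR) for each factor, set at 1.5, 2 or 3. The overall control rate is held at 20%, and a common treatment odds ratio brings the haloperidol arm to 10%.

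**4. Approximate size of the pooled test.** Let R² be the share of outcome variance explained by the strata: R² = Σ w(p − 0.20)² / 0.16, where w is the stratum share and p the stratum rate. With near-perfect balance within strata, the true size is about 2Φ(−1.96 / √(1 − R²)).

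| OR per factor | Control rates, lowest to highest stratum | R² | Approximate size |
|---|---|---|---|
| 1.5 | 16% to 29% | 0.011 | 4.9% |
| 2 | 13% to 37% | 0.033 | 4.6% |
| 3 | 9% to 48% | 0.080 | 4.1% |

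**5. Simulation.** 390 patients, 10:10 blocks of 20 within each stratum, last block possibly incomplete, 100,000 trials per case (Monte Carlo error about 0.1 point).

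| OR per factor | Size, Pearson v CMH | Power, Pearson v CMH | Power forgone |
|---|---|---|---|
| 1.5 | 4.9% v 5.0% | 80.1% v 80.3% | 0.2 points |
| 2 | 4.6% v 4.9% | 80.2% v 80.8% | 0.6 points |
| 3 | 4.1% v 5.0% | 80.6% v 82.3% | 1.7 points |

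Repeat runs of the same cases put the power difference between 0.1 and 1.8 points.

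**6. Sensitivity.**
- Strata not prognostic at all: size 4.97% v 4.94% and power 80.0% v 79.8%, so CMH costs about 0.2 points.
- A very steep gradient (control rates 7% to 50%, shares 15/35/15/35%): size 3.7% v 5.0% and power 81.3% v 84.2%, a gap of 2.9 points.
- Blocks kept separately at each of six sites: Pearson size between 5.1% (no prognostic effect) and 3.9% (widely spread rates). The CMH gain runs from about 0 to 3 points over the same range of gradients.

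**The case against.** The strongest case against the point is that it hardly matters. The planned test controls type I error, matches the test on which the sample size was computed, and reaches about 80% power in every case examined. At an odds ratio of 1.5 per factor the conservatism is barely detectable. A gain near 2 points needs control rates that run from about 9% to 48%, and the protocol supports the prognostic claim only in words. All of this stands, and it limits the point to a minor gain in efficiency.

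A reader might infer more than the documents support:
- *That the trial is underpowered because of this choice.* It is not. The pooled test delivers the planned power; the stratified test would deliver slightly more.
- *That the primary confidence interval will be too wide.* The Statistics section specifies no confidence interval for the primary outcome, so there is no stated interval to criticise.
- *That a stratified test would repair any remaining imbalance within strata.* CMH adjusts for unequal stratum membership between arms, such as unfinished blocks leave. It does not adjust for other covariates inside a stratum.

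One could also say that a separate analysis plan, not shown, may add an adjusted analysis. It may, but the article does not leave the primary test open. It names one, and that test is unstratified.

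**Conclusion.** The mismatch is in the text: the protocol stratifies on factors that it calls predictors of delirium and fixes a primary test that does not use them. The result is a valid, mildly conservative test. For odds ratios of 1.5 to 3 per factor, its true size is about 4.1 to 4.9% and it forgoes about 0.1 to 2 points of power.

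The direction follows from the design, provided the strata are prognostic as the protocol says. The size rests on assumed stratum shares and odds ratios, because the protocol gives none: it falls to essentially nothing if the strata are not prognostic, and reaches about 3 points only under very steep gradients. No conclusion of the trial is threatened. The change is worth making because it is nearly free and can be specified in advance.

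**What to change.** In the Statistics section, name the CMH test over the four age-by-planned-surgery strata, as used at randomisation, as the primary test. Report the Mantel-Haenszel risk difference with its 95% CI, and keep the crude Pearson chi-squared as a supportive analysis. The log-rank test for time to first delirium can be stratified in the same way.

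The stratum of each patient is already recorded at randomisation, so the cost is one sentence, with no extra data or patients. The worst case for power is a loss of about 0.2 points if the strata turn out not to be prognostic. The change should be fixed before unblinding.

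### The article names no baseline adjustment for the 3- and 6-month function and cognition scores, although baseline is measured: a valid analysis that gives away precision

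*Protocol article*

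**What the plan says.** Under Secondary outcome measures, the protocol article lists "cognitive and physical function at baseline, three, and six months post-discharge". Data collection names the scales: Katz ADL and Lawton IADL for physical function, 6-CIT for cognition. The Discussion adds that the 6-CIT is given face to face on admission. Follow-up assessments describes both post-discharge contacts in this way: "patients are contacted by telephone by one of the observers to perform the Katz ADL, the Lawton IADL scale, and the 6-CIT". The same three scales are therefore available before and after treatment.

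The Statistics section assigns tests by distribution. Student's t test is for continuous data that are normal. Of Mann–Whitney U the section says that it "is used for comparison of non-normal distributed data such as secondary outcome measures concerning efficacy of prophylactic haloperidol treatment". The section names no covariate, change score, ANCOVA, ordinal model or repeated-measures model, and it does not mention the three scales by name. They fall under the general class of secondary efficacy outcomes, and no other test in the section fits them.

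Under Randomisation, allocation is 1:1 within four strata formed by age (70 to 80, or 80 and over) and planned surgery on admission. Baseline function and cognition are not stratification factors.

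**The concern.** A patient's earlier score on a scale often predicts the later one. Where it does, a comparison that leaves it out counts stable between-patient differences as noise. Here the baseline is already collected, so the loss is avoidable. Three scales at two time points make six comparisons that could gain.

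The sample size was set for delirium incidence alone, so nothing in the design secures power for these scores. The Background says that existing non-drug programmes do not seem to change post-discharge cognition or function, and the Discussion promises evidence on post-discharge outcomes. Precision on these scores therefore matters to what the trial sets out to learn.

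**Working it through.** **The plan's own figure.** The only sample-size figure concerns the primary outcome: 20% against 10%, two-sided alpha 0.05, 195 per arm, which "will give us a power of 80% to detect differences". With z-values 1.960 + 0.842 = 2.802:
- Unpooled variance: (0.16 + 0.09) × 2.802² / 0.10² = 196 per arm.
- Pooled variance: 199 per arm. Arcsine: 194.9, that is 195.
- Power at 195 per arm: 79.2%.

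The stated figure reproduces and is not in question. The article gives none for function or cognition.

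**Inputs for the check.** 195 per arm and alpha 0.05 come from Sample size calculation. The correlation r is an assumption, shown from 0.3 to 0.7.

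**Gain from linear adjustment.** Adjusting for a baseline score with correlation r multiplies the residual variance by 1 − r². The equivalent sample multiplier is 1/(1 − r²). The difference detectable with 80% power is 2.802 × √(2/195) = 0.284 SD unadjusted, and that value times √(1 − r²) adjusted.

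| assumed r | 1 − r² | sample multiplier | detectable difference (SD) |
|---|---|---|---|
| unadjusted | 1 | 1 | 0.284 |
| 0.3 | 0.91 | 1.10 | 0.271 |
| 0.5 | 0.75 | 1.33 | 0.246 |
| 0.7 | 0.51 | 1.96 | 0.203 |

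The multiplier does not depend on how many patients are interviewed. With an assumed 156 per arm (20% without a score), the detectable difference is 0.317 SD unadjusted and 0.303, 0.275 and 0.227 SD adjusted.

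**Check against the test actually named.** In 3,000 simulated trials per setting, with normal scores, 195 per arm and an assumed true effect of 0.3 SD, Mann–Whitney had power of about 82%. ANCOVA had 92% at r = 0.5 and 99% at r = 0.7. A small part of that gap comes from using a linear test on normal data: the unadjusted linear comparison has 84.2% by formula. The rest is the baseline.

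**If change from baseline were ranked instead.** The article does not exclude this. With equal variances at both times, a change score has variance 2(1 − r) relative to the follow-up score: 1.40 at r = 0.3, 1.00 at r = 0.5 and 0.60 at r = 0.7. Because 1 − r² = (1 − r)(1 + r), adjustment is never worse than the change score on this measure. The variance ratio of change score to adjustment is 2/(1 + r): 1.54, 1.33 and 1.18. The suggestion holds under either reading.

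**The case against.** The best case for the plan has four parts.

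- **The unadjusted test is valid.** This stands. Under 1:1 stratified randomisation, chance imbalance at baseline is already covered by the type I error rate. An imbalance that happens to occur still moves the unadjusted estimate, but that is a question of precision.
- **The article does not say that raw follow-up scores are ranked.** This stands as a matter of wording. As shown above, it does not remove the gain.
- **The size rests on an assumed correlation.** This stands, and r may be low for the 6-CIT: baseline is taken during acute illness, and follow-up is by telephone, for which the article says the test is not validated. At r = 0.3 the gain is only 10%. The factor 1 − r² is also a linear-model result and only a guide for a proportional-odds model.
- **An unseen analysis plan may adjust.** It may. But the article names tests for this class of outcome, so the point concerns a stated method and not a silence.

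A reader might also infer that the plan analyses only survivors, since a patient who has died cannot be interviewed. The document does not support that. It promises intention-to-treat analysis of all randomised patients and gives a rule for death on the primary outcome only. How deaths are scored on secondary scales is commonly left to the full protocol or analysis plan, which are not shown. Nor would such a problem come from the rank test, which can place deaths at the worst rank; baseline adjustment alone would not cure it. Any bias is conditional as well. With no effect on function and 20% mortality in both arms (assumed), a survivors-only Mann–Whitney test rejected in 4.6% of simulated trials. It reached 10.4% only under an assumed 20% against 10% mortality and an assumed latent function–death correlation of 0.5.

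**Conclusion.** The point holds as an efficiency improvement for secondary outcomes. The tests named take no covariate, although baseline values of the same scales are collected. Linear adjustment would be worth about 1.1 times the sample at r = 0.3 and 2.0 times at r = 0.7. These correlations are assumptions; the article gives none. Type I error, the primary analysis and the sample size are untouched. No finding is made about the handling of deaths.

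**What to change.** State in the analysis plan, before unblinding, that each Katz ADL, Lawton IADL and 6-CIT score at three and six months is analysed by a model with treatment, the baseline value of the same scale, and the two randomisation factors (age group and planned surgery). A proportional-odds model keeps the ordinal character of the Mann–Whitney comparison and suits scores expected to be non-normal; ANCOVA is the simpler choice where linearity is reasonable. The unadjusted test can be kept as a supporting analysis.

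The cost is a change of wording and a little more analysis, with no extra patients or data. The downside is a model assumption, proportional odds or linearity, which should be checked and reported. An analysis that ranks death as the worst category may be added as a sensitivity analysis; this is optional.
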